# Efficacy of high-dose versus low-dose vitamin D supplementation on serum levels of inflammatory factors and mortality rate in severe traumatic brain injury patients: study protocol for a randomized placebo-controlled trial

**DOI:** 10.1186/s13063-020-04622-6

**Published:** 2020-07-29

**Keywords:** Traumatic brain injury, Vitamin D, Inflammation, Mortality

## Abstract

**Background:**

Traumatic brain injury (TBI) is the most common trauma worldwide and is a leading cause of injury-related death and disability. Inflammation is initiated as a result of the TBI, which is in association with severity of illness and mortality in brain trauma patients, especially in subdural hemorrhage and epidural hemorrhage cases. A high percentage of adults admitted to the intensive care unit with TBI are diagnosed with vitamin D deficiency; this deficiency may induce impaired immune responses and increase the risk of infections. Vitamin D intervention has been shown to modulate pro- and anti-inflammatory cytokines in non-critically ill patients, but to date, there is no substantial data on the effectiveness of vitamin D for the improvement of immune function in traumatic brain injury patients.

**Methods/design:**

A randomized clinical trial (RCT) will be performed on 74 Iranian adults 18–65 years old with brain trauma and will be treated daily with vitamin D supplements (100,000 IU oral drop) or a similar placebo (1000 IU) for 5 days.

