### Study objectives and rationale

The primary goal of the present study is to investigate the effect of daily intake of high-dose vitamin D (cholecalciferol) supplements (100,000 IU) versus low-dose vitamin D supplements (1000 IU) on mortality rate and inflammatory markers through a double-blind, randomized, controlled clinical trial on TBI patients. According to previous observational studies, TBI patients with vitamin D deficiency had higher mortality rate and neuroinflammation in comparison with TBI patients with vitamin D sufficiency [15, 17]. Also, as vitamin D deficiency is highly prevalent in critically ill patients, rapid normalization of this deficiency may be beneficial to these patients [7, 19, 20]. For this reason, we hypothesized that rapid correction of vitamin D deficiency in TBI patients may improve inflammation and decrease mortality rate. This study will also evaluate seven secondary outcomes that may be influenced by vitamin D administration in neurocritical patients. In order to determine the effects of high-dose vitamin D intervention, (1) Glasgow Coma Scale (GCS), (2) time of final weaning, (3) time of discharge from ICU, (4) SOFA (Sequential Organ Failure Assessment) score, (5) APACHE II (Acute Physiology and Chronic Health Evaluation II) score, (6) delirium severity, and (7) parathyroid hormone (PTH) test will be assessed in the treatment group compared to the control group. The study participants will be recruited from adult wards at trauma referral hospitals namely Kamyab and Taleghani in Mashhad, Iran. This study is a phase II RCT, and it has started from August 2019 and will carry on for 5 months.

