### Study design and setting

We will include 74 TBI patients with epidural hemorrhage (EDH), subdural hemorrhage (SDH), and subarachnoid hemorrhage (SAH) as diagnosed according to computed tomography (CT) scan or magnetic resonance imaging (MRI) findings by the neurosurgeon. Patients will receive vitamin D (cholecalciferol) drop (100,000 IU) or 1000 IU identical control drop in a 1:1 ratio through random assignment method. Vitamin D drops are manufactured by Zahravi Company under good manufacturing practice (GMP). Each vial of vitamin D drop is produced to be dissolved completely in 1 ml of extra virgin olive oil (Familia Company), through a nasogastric tube (NGT) for 5 days in TBI patients. Both high-dose and low-dose drops will have the same bottle, flavor, and aroma to the blinded.

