## Discussion

In the present study, if vitamin D significantly reduces the rate of mortality and inflammation in TBI patients, it can potentially provide the background for larger and well-designed multicenter clinical trial studies to establish the effect of vitamin D supplementation on TBI patients. Furthermore, vitamin D treatment is inexpensive and safe with minimal side effects and also could have positive impacts on critically ill patients (such as decreased mortality rate and hospital length) according to previous studies [7, 13, 14, 23, 24]. Potential limitations of the proposed study are as follows: measurement of vitamin D3 concentration with the chemiluminescence test instead of the gold standard method (liquid chromatography-tandem mass spectrometry). Another limitation is TBI patients’ blood transfusion because of trauma and bleeding; some TBI patients may require blood transfusion during the study, which may affect the biochemistry outcomes. Albumin injection in hypoalbuminemia patients can affect the levels of serum albumin. Also, TBI patients may need to undergo other surgeries than brain surgery; thus, this factor could affect the study outcomes. For this reason, we will compare mortality rate and inflammatory cytokine levels in all participants (intervention and control) and separate patients with anemia and hypoalbuminemia in each group. If the rate of death or inflammation in patients with anemia and hypoalbuminemia is different from those in the case or control group, the results will be reported separately. Based on recent studies, we have considered the suggested vitamin D dose (100,000 IU/day for 5 days) by Han et al. [23], as it is shown to be safe and efficacious in critically ill patients. Therefore, we believe that the present study could elaborate the necessity of vitamin D treatment and its efficacy on TBI patients at ICU.

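### The control is 1000 IU of vitamin D, not a placebo, so the trial can test high against low dose but not whether vitamin D is needed or how it compares with none

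*Protocol article*

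**What the plan says.** The article describes its control in two ways.

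- **As a placebo.** The title ends "study protocol for a randomized placebo-controlled trial". The methods paragraph of the abstract sets the 100,000 IU supplement against "a similar placebo (1000 IU" and uses the term vitamin D supplement for the higher dose only.
- **As low-dose vitamin D.** The same title opens "Efficacy of high-dose versus low-dose vitamin D supplementation". Study objectives and rationale compares the high dose "versus low-dose vitamin D supplements (1000 IU) on mortality rate and inflammatory markers". Study design and setting allocates patients to the high-dose drop or a "1000 IU identical control drop in a 1:1 ratio", given "through a nasogastric tube (NGT) for 5 days", and adds: "Both high-dose and low-dose drops will have the same bottle, flavor, and aroma". The purpose statement in the Background and both endpoint sections also speak of high and low dose.

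On interpretation, the Discussion ends by saying that the study "could elaborate the necessity of vitamin D treatment and its efficacy on TBI patients at ICU". The Conclusion then presents vitamin D treatment, with no dose named, as a possible new approach to care.

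**The concern.** A product containing 1000 IU of the study drug is not a placebo. The title and abstract thus give the trial a design property that its methods do not have, and they are the most widely read parts of the article.

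The label also matters for interpretation. With a true placebo arm, the trial could speak to vitamin D against none. With a low-dose arm it can speak only to the difference between two doses. The closing sentences of the Discussion and Conclusion are written in terms of vitamin D treatment as such, which fits the placebo label better than the design. At stake is what either a positive or a null result may be said to show.

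**Working it through.** The plan gives no figure to reproduce on this point. The check is a comparison of sections, followed by the logic of the contrast.

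**1. What each section calls the control**

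| Section | Description of control |
|---|---|
| Title, second half | placebo |
| Abstract, methods | placebo, with 1000 IU in brackets |
| Title, first half | low-dose vitamin D |
| Background, purpose | low dose |
| Study objectives and rationale | low-dose vitamin D, 1000 IU |
| Study design and setting | 1000 IU control drop; low-dose drop |
| Primary and secondary endpoints | low-dose vitamin D group |

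Only the title's design label and one abstract phrase say placebo, and the abstract phrase prints the active content beside the word.

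**2. Exposure in each arm**

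Inputs: 100,000 IU or 1000 IU daily for 5 days (Abstract); 37 patients per group (Sample size).

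- High dose: 5 x 100,000 = 500,000 IU
- Control: 5 x 1000 = 5,000 IU
- Ratio: 500,000 / 5,000 = 100
- Daily difference: 100,000 - 1000 = 99,000 IU
- Patients planned to receive no study vitamin D: 0 of 74

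**3. What the randomised comparison identifies**

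Let H, L and N be the mean outcomes under high dose, low dose and no vitamin D. Then

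H - N = (H - L) + (L - N).

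The trial estimates H - L. It has no data on N, so neither L - N nor H - N can be estimated.

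- **Positive result (H better than L).** This is a valid randomised effect of the added 99,000 IU per day. If the low dose also helps, H - L is smaller than H - N, so low-dose activity shrinks the contrast and does not create a false benefit.
- **Null result (H equal to L).** This fits H = L = N (no effect) and also H = L with both better than N (both doses act alike). The trial cannot separate the two.
- **Necessity.** Asking whether treatment is needed is a question about N, which is not observed. Moreover, entry requires a level below 20 ng/ml (Inclusion criteria), and the Safety section says deficiency at that level calls for treatment. The need for treatment is a premise of the design, not something it tests.

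**The case against.** The best defence is that nothing is hidden. The title names the dose comparison in its opening words, the abstract prints the 1000 IU, and the purpose and primary goal already state high against low dose. The hypothesis concerns rapid correction of deficiency, which a dose contrast can address. The broad closing sentence is hedged, the Conclusion is conditional, and both the abstract and the opening of the main Discussion limit a positive result to grounds for a larger multicentre trial. A blinded comparison of two doses of one drug is a recognised design.

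All of this stands, and it limits the point to the label and the breadth of the conclusions. It does not remove the point: the title and abstract still state something untrue of the comparator, and no hedge makes necessity testable without an untreated arm.

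A reader might go further in three ways that the documents do not support:

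- **That the trial can support no efficacy conclusion at all.** It can. Superiority of the high dose would be sound evidence for the added dose.
- **That the planned effect of 0.5 should be shrunk to allow for activity of the low dose.** The Sample size section defines 0.5 as the IL-6 difference between the two groups, so it is already the high-against-low contrast. The documents also give no figure for the activity of the low dose.
- **That the registry entry needs the same correction.** Its wording is not in the documents.

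**Conclusion.** The placebo wording in the title and abstract is wrong as written. The comparator is a low-dose active control, both arms receive vitamin D, and the trial identifies only the high-against-low contrast. It cannot show that vitamin D treatment is needed, nor its effect against none, and a null result would be ambiguous between no effect and equal effects.

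The size is one of labelling and interpretation: no dose, endpoint, analysis or sample size is affected. The conclusion rests on the article's own description of the two drops and on no assumption about how active 1000 IU is. It is more than clerical, because the label names the comparator and so sets what the trial may claim.

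**What to change.** - In the title and abstract, replace the placebo wording with low-dose active control.
- In the Discussion and Conclusion, limit the claims to high against low dose and remove the statement about necessity.
- Add one sentence saying that the effect of vitamin D against no vitamin D is not estimated and that a null result would not show vitamin D to be inactive.

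Trial status reports recruitment as complete, but these changes can still govern how the results are titled and interpreted. The cost is a few edits and a narrower claim. Conduct and doses do not change.

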**Discussion:**

If this randomized clinical trial demonstrates reductions in inflammatory cytokines, it would provide evidence for a multicenter clinical trial to evaluate the efficacy of vitamin D supplementation in neurocritically ill patients. Since vitamin D supplements are inexpensive and safe, this clinical trial could have the potential to improve clinical outcomes in traumatic brain injury patients through reduction of inflammation and infection-associated morbidity and mortality rates.

**Trial registration:**

Iranian Registry of Clinical Trials, IRCT20180619040151N3. Registered on 10 August 2019.

## Background

Vitamin D is an essential hormone for calcium homeostasis and its intestinal absorption. It also has an important role in several neuromuscular activities and metabolic responses [1]. Recent studies indicated that the active form of vitamin D (calcitriol) may have a crucial function in modulating immune responses to inflammatory conditions and infectious diseases [2, 3]. According to previous data, vitamin D deficiency has been associated with a high incidence of adverse events and mortality in critically ill patients [4]. Vitamin D can induce production of anti-inflammatory cytokines and some antimicrobial proteins such as cathelicidin by macrophages and neutrophils [3]. Antimicrobial proteins are expressed significantly in the respiratory epithelium and other organs, and they could reduce risk of infections in integumentary barrier sites [5, 6]. Notably, infectious diseases such as pneumonia and sepsis are common in traumatic patients leading to more than 20% rate of death in these patients; in addition, there is a high prevalence of vitamin D deficiency in these patients; therefore, vitamin D treatment is of high importance in traumatic brain injury (TBI) patients [7–9]. Moreover, vitamin D deficiency is also related to serious complications such as coma, slow neurological recovery, and critical illness polyneuropathy in TBI patients [10, 11]. Although there has been a direct association between vitamin D deficiency and adverse clinical outcomes in critically ill patients, the data regarding vitamin D supplementation from randomized clinical trials are limited [12]. In addition, vitamin D supplementation has not been shown whether it efficiently affects the endpoints of TBI patients or not [4, 9]. The type of vitamin D supplement, route of intervention, and speed of normalization may be associated with clinical outcomes in critically ill patients [4, 9, 12]. As compared to vitamin D injection, enteral vitamin D administration seems to be more effective and is considered safe [13, 14]. To date, studies on the effects of vitamin D on TBI patients have been inadequate and could not provide definitive conclusions [15–17]. The purpose of the present study is to determine the effect of high-dose vitamin D (cholecalciferol) supplementation versus low dose on mortality rate and inflammatory cytokine levels, in critically ill TBI patients under enteral nutrition therapy at intensive care unit (ICU).

## Methods/design

### Study design

The treatment of vitamin D deficiency in neurocritically ill patients (VITdAL-ICU) protocol is designed according to the CONSORT guidelines for randomized clinical trial (RCT) [18]. The protocol of this RCT is approved by the Medical Ethics Committee of Mashhad University of Medical Science (IR.MUMS.MEDICAL.REC.1397.381) and is registered at the Iranian Registry of Clinical Trials under IRCT20180619040151N3. The flow diagram illustrates details of the current study protocol in Fig. 1. Moreover, the study time framework for screening, supplementation, and monitoring is described in Fig. 2.

**Fig. 1 Fig1:**
[figure not shown]
Participant flow diagram according to the Consolidated Standards of Reporting Trials (CONSORT) 2010 statement

**Fig. 2 Fig2:**
[figure not shown]
SPIRIT figure showing the schedule of interventions and assessments. IL-6, interlukine-6; MCP-1, monocyte chemoattractant protein-1; CRP, C-reactive protein; PTH, parathyroid hormone; GCS, Glasgow Coma Scale; BMI, body mass index; FFM, fat-free mass; FM, fat mass; APACHE II, Acute Physiology and Chronic Health Evaluation II; SOFA, Sequential Organ Failure Assessment; MV, mechanical ventilator

### Study objectives and rationale

The primary goal of the present study is to investigate the effect of daily intake of high-dose vitamin D (cholecalciferol) supplements (100,000 IU) versus low-dose vitamin D supplements (1000 IU) on mortality rate and inflammatory markers through a double-blind, randomized, controlled clinical trial on TBI patients. According to previous observational studies, TBI patients with vitamin D deficiency had higher mortality rate and neuroinflammation in comparison with TBI patients with vitamin D sufficiency [15, 17]. Also, as vitamin D deficiency is highly prevalent in critically ill patients, rapid normalization of this deficiency may be beneficial to these patients [7, 19, 20]. For this reason, we hypothesized that rapid correction of vitamin D deficiency in TBI patients may improve inflammation and decrease mortality rate. This study will also evaluate seven secondary outcomes that may be influenced by vitamin D administration in neurocritical patients. In order to determine the effects of high-dose vitamin D intervention, (1) Glasgow Coma Scale (GCS), (2) time of final weaning, (3) time of discharge from ICU, (4) SOFA (Sequential Organ Failure Assessment) score, (5) APACHE II (Acute Physiology and Chronic Health Evaluation II) score, (6) delirium severity, and (7) parathyroid hormone (PTH) test will be assessed in the treatment group compared to the control group. The study participants will be recruited from adult wards at trauma referral hospitals namely Kamyab and Taleghani in Mashhad, Iran. This study is a phase II RCT, and it has started from August 2019 and will carry on for 5 months.

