### Randomization and blinding

Block randomization method will be considered for this trial study. TBI patients will be randomized (in four blocks) into the intervention group and control group based on a blinded randomization list generated and online databases for clinical trials (https://www.sealedenvelope.com) and will be managed by the research director of Clinical Nutrition Department, Mashhad University of Medical Sciences. Patients will be allocated by random according to the severity of brain injury (GCS 7–8 and 8–9), type of brain injury (EDH, SDH, and SAH), gender, and age to ensure match distribution of these factors in all four blocks. Given that the ICU supervisor has no knowledge of which vial contains high dose or low dose of vitamin D, TBI patients will be randomized to group A or B. The label A or B on vials will be deleted by the research director before allocating the study supplements; thus, the medication will appear similar to the study researcher and nurses. The TBI patient’s study identification code will be documented, and the intervention group may only be determined by comparing the patient’s study number to the reference blinded list, which only the research director will have access to until the trial is finished. Figure 2 indicates the SPIRIT schedule of evaluations and interventions.

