### Primary efficacy endpoint

The primary efficacy outcome for this trial will be assessed by comparing the changes in vitamin D levels and inflammatory markers (IL-6, monocyte chemoattractant protein-1 (MCP-1), and C-reactive protein (CRP)) between two groups. The rate of mortality in TBI patients until 28 days after admission (in ICU and regular ward) will be assessed in high- and low-dose vitamin D supplement groups. The impact of high dose versus low dose of vitamin D will be analyzed, with and without adjustment for age, sex, type of brain injury, and severity of injury. If the results differ after adjusting for the variables, the results of both analyses will be reported.

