### Secondary efficacy endpoints

All analyses will be conducted with and without adjustment for age, sex, type of brain injury, and severity of the injury. Time to event analysis will be analyzed similarly as the primary endpoint. The secondary outcomes are listed below:
Comparison of GCS score changes between the intervention and control groups during ICUComparison of APACHE II and SOFA scores between the intervention and control groups during ICUComparison of incidence of delirium between the intervention and control groups during ICUComparison of changes in PTH levels between the intervention and control groups during ICUComparison of time of discharge from ICU in patients treated with high-dose and low-dose vitamin D groups (during the first 28 days of admission)Comparison of time to weaning from mechanical respiratory support in patients treated with high-dose and low-dose vitamin D groups (during the first 28 days of admission)Comparison of need for a tracheostomy between the intervention and control groups during ICU stayComparison of occurrence of infections among the intervention and control groups during ICU stay

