### Study assessments

At the beginning of the trial, demographic information, anthropometric parameters (weight (bed scale, Balas Company), estimating height from ulna length), mid arm circumference (measured by tape at the mid-point between the tip of the shoulder and the tip of the elbow), fat-free mass and fat mass (bioelectrical impedance analysis s10, InBody Company), vitamin D3 status (25-hydroxy vitamin D3, chemiluminescence method), IL-6 (ELISA kit), MCP-1 (ELISA kit), quantitative CRP (ELISA kit), PTH (ELISA kit), Ca, APACHE II score, SOFA score, and delirium score will be measured and repeated on days 7 and 14 after intervention in groups A and B. All drugs will be ordered daily upon physician’s request during ICU stay and will be recorded. For adjusting the effect of energy on final outcomes, based on ESPEN guideline for all patients, 25 kcal/kg actual body weight energy is considered [21]. Moreover, the total kilocalories and macronutrient delivered by enteral feeding will be calculated daily for all the participants. Blood samples (5 ml) will be collected at baseline (ICU admission) and 7 and 14 days after intervention at 10:00 am. Blood sample will be taken from veins and centrifuged at room temperature, then stored at − 20 °C. Finally, the samples will immediately be transferred with the cold box to a freezer − 80 °C for future inflammatory cytokine measurements. All routine biochemistry, hematology, and urine tests, until day 14, will be measured after sampling in Kamyab Hospital Lab, Mashhad, Iran. Serum IL-6, MCP-1, and CRP levels will be analyzed in the baseline and days 7 and 14 at the Immunology Lab of Bu Ali Research Institute, Mashhad, Iran. In addition, in case of occurrence of infections (blood stream, the urinary tract, the gastrointestinal tract, wounds, and the lung), an internist specialist will take responsibility [22]. A summary of the schedule of registration, supplementation, and study evaluation is shown in Fig. 3.

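### Patients come from two hospitals, but the adjustment variables named for the primary and secondary endpoints leave hospital out, at a small cost in precision

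*Protocol article*

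**What the plan says.** **Recruitment.** Study objectives and rationale names two sites: participants will be "recruited from adult wards at trauma referral hospitals namely Kamyab and Taleghani in Mashhad, Iran".

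**Allocation.** Randomization and blinding states: "Patients will be allocated by random according to the severity of brain injury". It gives two GCS bands for severity and then adds "type of brain injury (EDH, SDH, and SAH), gender, and age to ensure match distribution of these factors in all four blocks". Hospital is not among these factors.

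**Analysis.** Under Primary efficacy endpoint, the effect of dose is analysed "with and without adjustment for age, sex, type of brain injury, and severity of injury". Secondary efficacy endpoints opens with the same list: "All analyses will be conducted with and without adjustment for age, sex, type of brain injury, and severity of the injury". Hospital is absent from both. Proposed analysis names t, Mann-Whitney, chi-square, Fisher and log-rank tests, and ANOVA or ANCOVA, and mentions no site term.

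**Status.** Trial status reports that recruitment was completed on 21 December 2019, so only the analysis can still be changed.

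**The concern.** Hospital is known at baseline and cannot be affected by treatment. Several endpoints are, or follow from, decisions by the treating unit: time to weaning, time to ICU discharge and tracheostomy. Infection and 28-day mortality may also differ between units. If outcomes do differ by hospital, two things follow for the adjusted analyses. Between-hospital variation that one term could remove stays in the residual of the continuous outcomes. And if the arms happen to differ in hospital mix, the adjustment variables named do not correct for it.

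The article is not silent on covariates. It spells out one list and applies it to the primary and to all secondary endpoints, so an analysis that followed the text would leave hospital out. At stake is some precision in a trial of 74 patients.

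**Working it through.** The plan gives no figure on hospital, so there is none of its own to reproduce on this point.

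**Inputs from the article:** 74 patients, 37 per arm, 1:1 allocation; 62 evaluable (31 per arm); planned effect 0.5 for IL-6.

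**Assumed, because the article does not give them:** the share p of patients from one hospital, and the hospital difference h in within-hospital SD units. Ranges used: p = 0.5 or 0.1; h = 0.3, 0.5, 0.8.

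**1. Value of adjusting, continuous outcomes.** The share of variance explained by hospital is R² = h²p(1−p) / (1 + h²p(1−p)). The extra patients that an unadjusted analysis would need for equal precision are 74/(1−R²) − 74 = 74 × h²p(1−p).

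| h | h² × 0.25 (equal split) | R² | extra patients | h² × 0.09 (10/90 split) | R² | extra patients |
|---|---|---|---|---|---|---|
| 0.3 | 0.0225 | 2.2% | 1.7 | 0.0081 | 0.8% | 0.6 |
| 0.5 | 0.0625 | 5.9% | 4.6 | 0.0225 | 2.2% | 1.7 |
| 0.8 | 0.1600 | 13.8% | 11.8 | 0.0576 | 5.4% | 4.3 |

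**2. Chance imbalance.** With an equal split, the SD of the between-arm difference in hospital share is √(2 × 0.25/37) = 0.116, or about 12 percentage points (0.117 by the exact hypergeometric calculation). An imbalance of one SD then shifts an unadjusted mean difference by 0.116 × 0.3 = 0.03 SD to 0.116 × 0.8 = 0.09 SD. With a 10/90 split the exact SD is 0.069, and the shift is 0.02 to 0.06 SD.

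Probability of a difference of at least 15 points, allocation not stratified by hospital:

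| Share from smaller hospital | 74 patients | 62 patients |
|---|---|---|
| 50% | 16% | 31% |
| 30% | 20% | 27% |
| 20% | 8% | 11% |
| 10% | 1% | 2% |

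The rise from 16% to 20% in the 74-patient column reflects the discreteness of the counts.

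**3. Power.** Adjustment reduces the residual SD to √(1−R²). With 31 per arm:

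| R² | effect 0.5 | effect 0.71 |
|---|---|---|
| 0 | 50.3% | 80.0% |
| 2% | 51.1% | 80.8% |
| 5% | 52.4% | 82.0% |
| 10% | 54.6% | 84.0% |

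The gain is about 1 to 4 points. The second column is there because 31 per arm gives 80% power only at an effect of about 0.71. For an effect of 0.5 at two-sided 0.05, the article's formula gives 2 × (1.96 + 0.84)²/0.5² ≈ 63 per arm. That is a separate matter, and nothing here rests on it.

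**4. Which outcomes this covers.** Primary efficacy endpoint compares changes in vitamin D, IL-6, MCP-1 and CRP. A constant hospital offset in level cancels in a within-patient change, so for these endpoints h would have to be a hospital difference in change. For binary and time-to-event outcomes there is no residual error term. Omitting a prognostic factor there mainly attenuates the estimated effect, and the patient counts in step 1 do not carry over directly.

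**The case against.** The strongest reply is that the document contradicts nothing here and that the size is wholly assumed. It describes no difference in care between the hospitals, refers to the ICU supervisor in the singular, and sets one energy target for all patients. The split is unknown; if one hospital supplied few patients, the gain would be negligible. The four variables are not said to be the only ones, and site terms are often left to an analysis plan, which is not shown. Randomisation keeps the unadjusted tests valid, and their type I error already allows for chance imbalance. All of this stands as a limit on importance. It does not remove the point, because the article chose to list its covariates, twice, and a known baseline variable is missing from the list.

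Three stronger readings are tempting and are not supported:

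- **Sample handling.** A reader might infer that samples from the second hospital travel further, because routine tests "will be measured after sampling in Kamyab Hospital Lab, Mashhad, Iran". That sentence covers routine biochemistry, hematology and urine tests. IL-6, MCP-1 and CRP are assayed at one separate research institute, after one described procedure. No distances are given, and the article does not say where the second hospital's samples are processed.
- **Noise everywhere.** A reader might infer that hospital inflates the error of all the comparisons. The chi-square, Fisher and log-rank tests have no such error term, and a constant offset drops out of the change endpoints.
- **Bias.** A reader might infer systematic bias between the arms. Randomisation rules that out; what remains is chance imbalance.

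**Conclusion.** The point holds as a minor one. Two hospitals recruit, and hospital is in neither the allocation factors nor the stated adjustment variables. Adding it would bring a modest gain in precision and some protection against chance imbalance. Under the assumed hospital differences of 0.3 to 0.8 SD, the gain for continuous outcomes equals about 2 to 12 extra patients with an equal split and about 1 to 4 with a 10/90 split. If the hospitals do not differ on an outcome, the gain is nil. The case is strongest for outcomes that may follow local practice and weakest for the marker changes. No result of the planned unadjusted tests is made invalid.

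**What to change.** - In Primary efficacy endpoint and Secondary efficacy endpoints, add hospital as one term to the adjusted analyses. Include the adjusted analyses of binary outcomes such as tracheostomy and infection. The unadjusted analyses stay as they are.
- Stratify the log-rank tests for mortality, weaning and ICU discharge by hospital. State beforehand a minimum count per hospital below which the stratum is omitted, so that the choice does not depend on results.
- If the sponsor judges hospital unnecessary, for example because nearly all patients came from one site, say so and give the split.

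The randomisation cannot be changed now that recruitment is complete. A fifth allocation factor would in any case have made strata sparse with 74 patients.

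Cost: wording, one degree of freedom in each model, and a small loss of information in the stratified log-rank tests. No new data are needed beyond each patient's recruiting hospital, which is assumed to be on record.
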